### Inclusion criteria

Eligible patients are those (1) diagnosed with stroke and confirmed by computed tomography or magnetic resonance imaging; (2) first-ever clinical stroke occurred ≤ 6 months previously; (3) FMA-UE score of ≤ 33 points; (4) modified Ashworth score of grade II or lower; (5) aged between 18 and 80 years; (6) stable vital sign and consciousness; and (7) provided written informed consent to participate.

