### Outcome assessment

The study period is 16 weeks. Outcomes will be assessed at baseline, after 4 weeks of intervention, at 6-week follow-up, and at 12-week follow-up. All outcomes will be measured by several experienced assessors who are blinded to the randomization group after the baseline visit for evaluation. All assessors will be trained to administer these assessments.

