### Primary outcomes

The primary outcomes in this study are the mean change in the scores on both the FMA and WMFT from baseline to 4 weeks intervention and 12 weeks follow-up between the two groups and within groups.

The FMA is widely used for motor function assessment and can reflect the functional level of stroke subjects. Even during the early stage of functional recovery, it can distinguish the level of motor function, particularly for those who have low responsiveness. The upper extremity has a maximum score of 66 points divided into three parts, namely shoulder–arm (36 points), wrist–hand (24 points), and coordination (6 points). The FMA-UE is the most common scale for evaluating upper limb motor function after stroke. It is often used as a gold standard for testing the validity of other scales as well [16, 17]. The FMA-UE has excellent reliability and validity and is sensitive enough for clinical and research practice [18].

The WMFT is the preferred scale for assessing mandatory exercise therapy for improving upper limb functions. It can either assess the quality of the patient’s completion of each activity or determine the time required for the patient to do so. The WMFT has good reliability and validity and high internal consistency [19].

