### Data collection and management

The data will be entered into a carefully designed electronic CRF. A dependent research assistant (RA) will be in charge of quality control during the data collection process. The project leader will be responsible for the initial data cleansing, identification, coding, and conversion to the appropriate data analysis format. In addition, an independent data and safety monitoring board will be established to monitor the safety of the trial. It will comprise two professional therapists who are experienced in the rehabilitation of limb movement dysfunction after stroke and who are not directly involved in this study. The data and safety monitoring board is independent and will be responsible for the effectiveness and management of data and reports of adverse events.

Demographic information, medical history and medication, lesions, affected side, handedness, cognitive function, time since stroke, stroke type, rehabilitation history (treatment until the beginning of the study), details of current and upper limb dysfunction treatment received within the previous 3 months, and concomitant medications will be recorded. Data will be obtained through direct questions to patients or a relative or proxy and from medical records. The outcome measure will be performed by an experienced assessor after intervention and follow-up. All forms must be dated and signed by the responsible investigator or one of the authorized staff members.

The project manager will have access to the data, and all data is treated with utmost confidentiality and made anonymous to anyone outside the study. All researchers in this study will receive anonymous copies of all data in order to promote dissemination of study results. The result of our study will be published in a peer-reviewed journal.

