### Statistical analysis

All allocated subjects will be analyzed using the available data (i.e., on the basis of the intention-to-treat). A multiple imputation method will be used to complete missing data. Continuous variables will be expressed as mean (SD) for normal distribution or median for non-normal distribution, and categorical variables will be expressed as frequencies or percentages. A significance level of 95% (two-sided alpha *P* < 0.05) will be used.

After examining the data for normality (Kolmogorov–Smirnov test), the outcome measures will be analyzed using analysis of variance (assuming normal distribution) or Kruskal–Wallis (non-parametric). Demographic characteristics and other baseline values will be described using descriptive statistics for each group. Intragroup comparisons (changes in the FMA-UE, WMFT, VAS, SIS, and MBI scores before and after treatment) will be performed using the paired *t* test. The statistical significance of the observed differences between the groups will be assessed using 2 × 2 factorial analysis of variance to test the main effect and interaction effects of the two interventions (AT and MT). A statistician blinded to study groups will conduct statistical analysis.

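### The factorial ANOVA of change scores names no covariate, although baseline scores and time since stroke are collected: valid, but usually less precise than a factorial ANCOVA

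*Protocol article*

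**What the plan says.** The section that defines the primary outcomes reads: "The primary outcomes in this study are the mean change in the scores on both the FMA and WMFT from baseline to 4 weeks", and it adds the 12-week follow-up. Under Secondary outcomes, the VAS, SIS and MBI are also mean changes.

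Statistical analysis: the between-group test is a 2 × 2 "factorial analysis of variance to test the main effect and interaction effects of the two interventions (AT and MT". The same section gives a route for non-normal data: "the outcome measures will be analyzed using analysis of variance (assuming normal distribution) or Kruskal–Wallis (non-parametric". Neither sentence names a covariate. The use stated for baseline data is this: "Demographic characteristics and other baseline values will be described using descriptive statistics for each group". Missing data are to be handled by multiple imputation, with no imputation variables listed.

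The candidate covariates are already collected. Outcome assessment: "Outcomes will be assessed at baseline, after 4 weeks of intervention, at 6-week follow-up, and at 12-week follow-up". Data collection and management lists, among other items, "cognitive function, time since stroke, stroke type, rehabilitation history". The Inclusion criteria admit an FMA-UE score of up to 33 and a "first-ever clinical stroke occurred ≤ 6 months previously". The Randomization and allocation section names no stratification factor.

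**The concern.** Taking the difference from baseline adjusts for baseline with a slope fixed at 1. If the true slope of follow-up on baseline differs from 1, the residual variance is larger than it need be. Any chance difference in baseline between the groups then leaves part of itself in the estimate. Time since stroke may range from 0 to 6 months at entry and does not enter the model at all, so an imbalance in it stays in the comparison to whatever extent it predicts change.

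What is at stake is the width of the intervals and how far a single realized estimate depends on the luck of the allocation, with 34 patients per arm. It matters most for the AT × MT interaction. The Background makes synergy the first aim, and the interaction is the contrast with the largest chance imbalance.

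**Working it through.** **Inputs.** From the protocol: 34 per group and 136 in total; 112 before attrition, with effect size 0.3, two-sided α 0.05 and 80% power (Sample size; Statistical analysis). Assumed, because the documents do not give them: the correlation ρ between baseline and follow-up, taken as 0.5 to 0.9, and the ratio k of follow-up SD to baseline SD, taken first as 1.

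**Step 1. The plan's own figure.** Read 0.3 as Cohen's f and use the noncentral F distribution with λ = N f² and four cells. A numerator df of 2 requires N = 111, or 112 in four equal groups, which reproduces the stated 112 (power 80.7%). That df belongs to no single effect of a 2 × 2 design. For a 1-df main effect or interaction, f = 0.3 and N = 112 give 88.2%. Both settings are carried below as reference points only.

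**Step 2. Variance with equal SDs (k = 1).**
- Change score: 2σ²(1−ρ).
- ANCOVA on baseline: σ²(1−ρ²).
- Ratio: (1−ρ²) / [2(1−ρ)] = (1+ρ)/2.

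**Step 3. Chance imbalance in baseline, in baseline SD units (95% range).**
- Main effect, 68 against 68: ±1.96 × √(2/68) = ±0.34.
- Two cells, 34 against 34: ±1.96 × √(2/34) = ±0.48.
- Interaction, a difference of two cell differences: ±1.96 × √(4/34) = ±0.67.

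Given an imbalance δ, the change-score estimate is off by (ρ−1)δ when k = 1.

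**Step 4. Results.** Power uses f = 0.3/√[(1+ρ)/2], N = 112 and one covariate df.

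| ρ | Variance ratio | Equivalent sample (1/ratio) | Power, 1-df test (88.2% unadjusted) | Power, 2-df setting (80.7% unadjusted) | Size of error left by a 0.34 SD imbalance |
|---|---|---|---|---|---|
| 0.5 | 0.75 | 1.33 | 95.3% | 90.9% | 0.17 SD |
| 0.7 | 0.85 | 1.18 | 92.7% | 87.0% | 0.10 SD |
| 0.8 | 0.90 | 1.11 | 91.3% | 84.9% | 0.07 SD |
| 0.9 | 0.95 | 1.05 | 89.8% | 82.8% | 0.03 SD |

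**Step 5. Unequal SDs.** In general the ratio is k²(1−ρ²) / (1 + k² − 2ρk). At ρ = 0.7:
- k = 1: 0.51/0.60 = 0.85.
- k = 1.25: 0.797/0.8125 = 0.98.
- k = 1.4: 0.9996/1.00 = 1.00.

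The true slope is ρk. At k = 1.4 it is 0.7 × 1.4 = 0.98, so the fixed slope of 1 is almost right and nothing is gained. The baseline FMA-UE is capped at 33 of 66 by eligibility while follow-up scores are not, so k above 1 is plausible for that outcome.

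**Step 6. Cost in degrees of freedom.** With all 136 analyzed, residual df go from 136 − 4 = 132 to 130.

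**The case against.** The strongest reply is that nothing here is an error. A reader might infer that the planned ANOVA is biased or that its P values are wrong. The documents do not support that: allocation is randomized, regression to the mean affects all arms alike in expectation, and type I error is correct. That part of the reply stands, and the point is one of efficiency and of accuracy given the realized imbalance.

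A reader might also infer that baseline imbalance is ignored. For the outcomes themselves it is not. Subtracting baseline does correct it, but by a fixed amount that is right only when ρk = 1. Only for time since stroke is imbalance left wholly unaddressed, and the documents give no figure for how strongly that variable predicts recovery, so no gain from it is claimed.

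A third inference is that the trial lacks power because of this choice. At the protocol's own effect size, read as f = 0.3, a 1-df factorial test at 112 has 88.2% power without adjustment. Whether 0.3 is realistic is a separate question.

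It can also be said that this is a condensed article and that an analysis plan not shown may add covariates. The text does not exclude that. But it names the between-group model and assigns baseline values a descriptive use, so a plan that follows it would be unadjusted.

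Finally, a reader might look to a repeated-measures model by arm and visit with week 4 as the sole primary contrast. That would change the stated primary time points and, unless written in terms of AT, MT and AT × MT, would not test synergy.

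**Conclusion.** The point holds as a free improvement. The planned analysis is valid, but it leaves available baseline information out of the between-group model. With equal SDs, adjusting for baseline removes 25% of the variance at ρ = 0.5, 15% at 0.7, 10% at 0.8 and 5% at 0.9. With a larger follow-up SD the gain can fall to about nothing, as at k = 1.4 and ρ = 0.7. In large samples the adjusted analysis is no less precise than the change score, apart from the degrees of freedom spent. The size rests on ρ and k, neither of which the documents give, and the power figures rest also on reading 0.3 as Cohen's f for the change score.

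**What to change.** In Statistical analysis, keep the 2 × 2 model with AT, MT and AT × MT, and keep the primary time points as stated. Add two prespecified covariates, the baseline value of the outcome being analyzed and time since stroke, for FMA-UE, WMFT, VAS, SIS and MBI. The outcomes can remain changes from baseline: once baseline is in the model, analyzing the change or the follow-up value gives the same treatment estimates. Include the same covariates in the multiple imputation model. Say what happens to the adjustment if the Kruskal–Wallis route is taken, since that test carries no covariate.

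The cost is a few sentences and two model degrees of freedom; all the data are already collected. The change should be fixed before unblinding, so that covariates are not chosen with the results in view.

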### Quality control

Quality control of informed consent: We will randomly select 20% of the participants to determine their knowledge about the study and awareness of signed informed consent. If they are knowledgeable, then this procedure will pass. Otherwise, the trained RA will need to explain the study again to all participants and randomly select 40% of the participants to determine their knowledge. If they are knowledgeable, then the procedure will pass; otherwise, the trained RA will explain again.Quality control of participant screening: Participant screening must be performed according to the inclusion and exclusion criteria. If participants meet all the criteria, then this procedure will pass. On the contrary, participants who do not meet the criteria will be excluded, and the number and reasons will be recorded.Quality control of intervention: The project manager will supervise the AT therapist and MT therapist who will treat the participants, and the MT therapist will supervise the intervention process of the participants. At the same time, an independent inspector will review the trial process, including the treatment of the subjects, the procedures of the therapist, and the registration of adverse events.Quality control of statistical analysis: Missing data are not allowed in report forms, particularly for the security index, which must be recorded clearly. Basic demographic data, such as sex, date of birth, and date of inclusion, among others, should be recorded to distinguish between missing data. If the missing data are left out after checking the original data, then we need to complete the missing parts. If the missing data are the security index, then we will not record them in the original data for security; rechecking of data will be necessary. The security index will be removed if it affects the results.Quality control of data management: The project manager will preserve and check all file lists. If there are missing data, then related personnel will be required to complete what is missing. Then, we will randomly select 10% of the CRF to check whether there any data errors. All data will be independently double-entered into a computer. The CRF questionnaire will be submitted to the investigator via the clinical examiner for data auditing, and the investigator should reply as soon as possible thereafter.

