### Safety assessments

Acupuncture may cause discomfort or bruising at the sites of needle insertion, nausea, or feeling faint after each treatment. No adverse reactions caused by MT have been reported to date.

During the course of the study, any accidental injury and sudden illness will be recorded. The degree of symptoms, time of occurrence, duration, and treatment will be documented in the observation table. All adverse events reported should be analyzed regardless of the investigators’ assessments of causality. Serious adverse events will be reported to the ethics committee immediately.

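### Quality control: the rule that removes the undefined security index when it affects the results is outcome-dependent exclusion and should be deleted; the rules for completing missing data need reconciling with the planned imputation

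*Protocol article*

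**What the plan says.** The main text is in the Quality control section of the protocol article, under the item on statistical analysis. It makes four statements that bear on this point.

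- Completeness: "Missing data are not allowed in report forms, particularly for the security index, which must be recorded clearly".
- Blanks that remain after checking: "If the missing data are left out after checking the original data, then we need to complete the missing parts".
- A missing security index: "If the missing data are the security index, then we will not record them in the original data for security", followed by a call to recheck the data.
- Removal: "The security index will be removed if it affects the results".

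The item on data management in the same section adds: "If there are missing data, then related personnel will be required to complete what is missing".

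Two other sections cover the same ground. Safety assessments says: "All adverse events reported should be analyzed regardless of the investigators", with the sentence going on to refer to the investigators' view of causality. Statistical analysis says: "A multiple imputation method will be used to complete missing data", and includes all allocated subjects on the available data.

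The term security index occurs only in the Quality control section and is not defined there or in the abbreviations.

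**The concern.** A variable or record may properly be excluded for reasons fixed in advance that do not depend on the findings, such as a value that cannot be verified against source. Here the only stated trigger is that the item affects the results. Applied as written, the sentence would let the content of the analysis depend on what the analysis shows. No p-value, estimate or safety table produced under such a rule could be taken at face value, because a reader could not know what had been removed or why.

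If the item is safety data, the stake is more specific: recorded safety information could be left out of the report although another section promises that all of it is analysed.

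The completion rules raise a smaller concern. Multiple imputation treats a value as uncertain only if it is marked as missing. If staff wrote an unsourced value into the form, the imputation would take it as observed and its uncertainty would be lost. The text does not say that this will happen, but it does not exclude it.

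**Working it through.** No sample size, power or event count enters this point, so there is nothing to recompute. The check is a comparison of the passages.

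**1. The removal rule taken alone.** The condition is an effect on the results. The sentence gives no data-quality criterion, no threshold, no person who decides and no requirement to decide blind. The objection therefore holds for any meaning of security index.

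**2. The removal rule against its own paragraph.** The paragraph singles this item out as the one that above all must not be missing and must be recorded clearly. It then says that the item, if missing, will not be entered in the original data, and finally that it will be removed if it affects the results. An item cannot be both the one most strictly required and one that is discarded according to its influence.

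**3. The removal rule against Safety assessments.** That section records any accidental injury or sudden illness and analyses all reported adverse events whatever their presumed cause. If security index means safety data, the two sections contradict each other. The special emphasis on its completeness, in a section that also has an inspector review the registration of adverse events, makes this the likely reading. It remains an inference because the term is undefined.

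**4. The completion rules against Statistical analysis.** Two instructions are set against the imputation:

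| Place | Instruction | When | By whom | Limited to source? |
|---|---|---|---|---|
| Quality control, statistical analysis item | complete the missing parts | after the original data have been checked | not stated | no |
| Quality control, data management item | complete what is missing | when files are checked | staff concerned | no |
| Statistical analysis | multiple imputation | at analysis | statistician | not applicable |

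The first instruction takes effect once the original data have already been consulted, so it is hard to read as retrieval from source. The second gives the task to people rather than to a model. Neither says what happens to a value that cannot be found. The article therefore does not make clear which values reach the imputation as missing.

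**The case against.** The strongest reply is that the paragraph is garbled, perhaps in translation, and should not be read as a licence to delete data. The sentence just before the removal rule concerns a missing security index, so the rule may be meant only for missing or unverifiable entries. That is possible, but the stated test would still be the effect on the results and not whether the entry can be verified. The objection therefore does not rescue the sentence, though it is a good reason to ask first what the term means.

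On completion, the reply is stronger. The data management sentence sits among file checks, a check of 10% of the case report forms, double entry and data auditing, and reads naturally as query resolution. The other sentence uses the same verb as the imputation sentence and may refer to that step. Nothing directs staff to invent values. This part stands only as a request to reconcile the sections.

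The protocol also has safeguards: blinded outcome assessors, data manager and statistician, a code disclosed only after the analysis, a data and safety monitoring board, and an independent inspector. These limit deletion driven by knowledge of allocation. They do not cure a rule whose trigger is the results themselves.

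A reader might go further and infer a size and direction of bias. The document supports neither.

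- One might take 20% of 136, about 27 patients, as having outcomes that staff would supply. No section says that staff will enter scores for patients who leave the trial, and the protocol's own allowance is 136 − 112 = 24.
- One might say that treatment-related harms can arise only in the three active arms (3 × 34 = 102 patients), so that removal would favour the interventions. The article says no adverse reactions to mirror therapy have been reported, and needling takes place in two arms (2 × 34 = 68). Injuries and illnesses of any cause are recorded in all four arms, so the direction is conjecture.

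**Conclusion.** The removal sentence is wrong as written and should not stand. This conclusion rests on the wording alone and needs no assumption about what security index means. The contradiction with Safety assessments is likely but depends on reading the term as safety data. The mismatch between the completion rules and the multiple imputation is a secondary matter of ambiguous text. It assumes only that completing is not already confined elsewhere to source-verified entries, which the article does not say.

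The size and direction of any bias cannot be determined from the document. Nothing links the security index to the Fugl–Meyer or Wolf Motor Function Test scores, so an effect on the primary comparison is not shown either. The case for correction is that the rule is unsound in principle and easily removed. The article gives the trial status as ongoing recruitment, so on that basis the change can be made before the analysis.

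**What to change.** 1. Define security index, or replace it with the name of the variables meant.
2. Delete the removal sentence and state that no recorded value is removed because of its effect on any result.
3. Reword the completion rules in both items of the Quality control section: a blank is filled only from a source document, and a value that cannot be sourced stays missing and is handled by the multiple imputation described under Statistical analysis.
4. Keep the rule in Safety assessments that all reported adverse events are analysed, and make the Quality control section consistent with it.

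The cost is a few sentences in the protocol and the corresponding data-management instructions. Sample size, visits and interventions are unaffected.
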